### Data quality assurance

Data collectors will be recruited based on their experience with a minimum educational qualification of a BSc in nursing and public health officer. Also, supervisors will be recruited based on previous experience in data collection and supervision and a minimum qualification of an MSc or MPH degree. Training will be given to data collectors and supervisors for 1 day about the aim, methodology, sampling technique, ethical issues, and data collection instrument and procedure. Data collection tools will be judged by professional and language experts. The appropriateness of the tool will be checked by conducting a pretest, and the necessary amendments will be made based on the pretest results. Then, baseline data will be collected to compare the pre-and post-intervention findings of both intervention and control arms. The researcher will regularly communicate with the data collectors and supervisors, with face-to-face scheduled meetings and virtual meetings to discuss any issues that arise during the data collection. To minimize data entry errors, a double data entry method will be used. To avoid information contamination, the buffering zone will leave between the intervention and control clusters. Outcome measurements will be performed in the same manner in both arms. Training will be provided for the outcome assessor and the data will be analyzed using intention-to-treat principles [43]. To ensure methodological quality, a Consolidated Standards of Reporting Trials 2010 statement extension to cluster randomized control trial study guidelines will be used [44]. In addition, to ensure better reporting of the intervention, the template for the Intervention Description and Replication (TIDieR) checklist will be used to increase methodological quality [45].

### Data processing and management

In the field, data will be checked for consistency and completeness every day by supervisors and the principal investigator. Then, a data entry template will be created on EpiData version 4.6 based on coded responses. Data will be entered by data clerks using EPiData software about 10% will be randomly double-checked by the principal investigator. The data will be then exported to STATA version 14 for further analysis. Data coding and cleaning will be done to check for inconsistencies, outliers, and missing values. Finally, the cleaned data will be processed and analyzed using STATA. Before further processing of the data, numeric data will be checked for normality using normality plots (Q-Q plots and/or histograms) or normality tests.

### Data analysis

Descriptive statistics will be used to summarize the baseline data. A chi-square test will be performed to compare the baseline characteristics of the intervention and control groups. Comparisons of detection rate, diagnosis delay, and costs of TB care between and within the intervention and control groups will be done using independent samples and paired sample *t*-tests, respectively. The independent *t*-test will be also used for the knowledge and attitude of post-test results of practitioners.

Logistic regression analysis will be used to determine the factors associated with case detection rate and diagnosis delay. A univariable logistic regression model will be fitted, and variables having a *p*-value less than 0.25 in the univariable logistic regression model will be fitted into the multivariable models. Variables with a *p*-value < 0.05 in the multivariable logistic regression model can be considered statistically significant. Crude and adjusted odds ratio (OR) with 95% confidence interval (CI) will be calculated to measure the strength of association between the dependent and independent variables. The fitness of the logistic regression model will be checked using the Hosmer–Lemeshow goodness of fitness test at *p*-value > 0.05. Multicollinearity between explanatory variables will be checked by a variance inflation factor (VIF), and variables with a VIF > 5 will be excluded from the final models.

Generalized linear mixed models (GLMM) will be used to assess the impact of the intervention on the change of cost of TB care. This GLM enables us to accommodate the correlation of observations due to the pre and post-intervention measurements and clustering of individuals within randomly selected clusters. Model fitting will be checked before the analysis is done. The effects of potential confounding factors will be controlled. The variance of the cluster-level residual errors will be computed using the intercept-only model. The variation between and within the groups will be analyzed.

Subgroup analysis will be employed to explore whether there is evidence that the detection variation depends on certain patients or facility characteristics. Covariate adjusted analysis will also employ to refine the analysis of case detection variation in the intervention and control arms the fact that some baseline characteristics may be related to outcome and unbalanced between the groups.

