**Methods:**

A cluster randomized controlled trial will be conducted in northwest Ethiopia to determine the effectiveness of integrating traditional care with modern TB care. The intervention will be conducted in randomly selected districts in the South Gondar Zone. The control group will be an equal number of districts with usual care. The intervention comprised three key components, which include referral linkage from traditional to modern health care; training of health professionals and traditional care providers in three different rounds to increase their knowledge, attitude, and skills toward the referral systems; and TB screening at traditional health care sites. The primary outcomes of interest will be an increase in case detection rate, and the secondary outcomes of interest will be decreased diagnosis delays and catastrophic costs for TB patients. Data will be collected in both the intervention and control groups on the main outcome of interest and a wide range of independent variables. Generalized linear mixed models will be used to compare the outcome of interest between the trial arms, with adjustment for baseline differences.

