### Randomization and recruitment

Randomization will be done at the district level. There are thirteen districts and two town administrations. Among a total of districts and town administrations, six districts and/or town administrations in South Gondar Zone will be selected using the random.org software by considering the rule of thumb assumption that covers 40% of districts and town administrations. Thus, the selected districts/town administrations will be assigned to the intervention and control arms with a 1:1 allocation ratio. This means three districts or town administrations will be randomly assigned to the intervention arm, and the other three districts or town administrations will be assigned to the control arm. District or town size will not be considered in the randomization process. All health facilities in the intervention and control arms fulfilling the eligibility criteria will be included in the study. The eligibility criteria for the inclusion and/or exclusion of health facilities will be based on the availability of TB diagnostic and treatment services, including the microscope diagnostic service and DOT programs. Participants will recruit to the study when confirmed they have any form of TB and are registered to the DOT programs. Participants will enter into the trial individually based, and patients will recruit continuously until the desired sample size achieve. Recruitment of participants will be from July 1 to September 30, 2022. The statistician who allocated the intervention and control arms, an expert who assesses the outcomes, participants who will be assigned to intervention and control arms, and healthcare providers who provide TB care will not be aware of who were assigned to the intervention and control arms. The project manager and/or investigators will be unblinded.

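### Diagnosis delay is compared between arms without allowing for the randomised districts, the Data analysis section and the abstract disagree on the method, and the unit of analysis for case detection rate is not fixed

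*Protocol article*

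**What the plan says.** Under Randomization and recruitment: "Randomization will be done at the district level", and "three districts or town administrations will be randomly assigned to the intervention arm", with the other three going to control.

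The Data analysis section names these methods:

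- **Detection rate, delay and cost:** "Comparisons of detection rate, diagnosis delay, and costs of TB care between and within the intervention and control groups will be done"; the same sentence goes on to name the tests: "between and within the intervention and control groups will be done using independent samples and paired sample *t*-tests, respectively".
- **Case detection and delay:** "Logistic regression analysis will be used to determine the factors associated with case detection rate and diagnosis delay".
- **Cost:** "Generalized linear mixed models (GLMM) will be used to assess the impact of the intervention on the change of cost of TB care". This model is said to accommodate pre/post correlation and "clustering of individuals within randomly selected clusters".

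The abstract (Methods) is broader: "Generalized linear mixed models will be used to compare the outcome of interest between the trial arms, with adjustment for baseline differences". It does not limit the mixed model to cost.

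The Measurements section defines case detection rate as notified cases over estimated cases for a catchment population, so it belongs to an area and not to a patient. The sample size section for detection rate counts 40 clusters, 24 against 16, which does not match six randomised districts.

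**The concern.** Patients in one district share health facilities, access and care-seeking habits, so their delays are correlated. Only six units are randomised. A test that counts each patient as independent takes its standard error from patient-to-patient variation and leaves out the variation between districts. It therefore rejects too often when the intervention does nothing.

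Delay is the exposed outcome. It is measured per patient, so a patient-level t-test is the natural reading, and the Data analysis section gives it no clustered alternative. The delay and cost sample sizes point the same way: they describe an individually randomised trial and multiply by a design effect of 0.95, which is below 1.

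Cost has two methods, one clustered and one not, and no rule for which decides. Case detection rate has a t-test whose units are not stated. An ordinary difference between districts could be reported as an effect of the intervention.

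**Working it through.** **1. Reproduce the plan's figure for delay.** Inputs from the sample size section: 59.9% against 45.9%, alpha 0.05 (taken as two-sided), power 80%, non-response 10%. The usual two-proportion formula without continuity correction gives 199 per arm, or 398 in total. 398 × 1.10 = 437.8, which rounds to the stated 438. Then 438 × 0.95 = 416.1, the stated 416. The planned number is therefore clear.

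**2. Patients per district.** 416 / 6 = 69.3.

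**3. True error of a test that ignores district.** With DEFF = 1 + (m − 1) × ICC, the naive standard error is too small by a factor of √DEFF. The nominal 5% test then has type I error 2 × [1 − Φ(1.96 / √DEFF)].

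| ICC | Source | DEFF (m = 69.3) | 1.96/√DEFF | Type I error |
|---|---|---|---|---|
| 0.05 | protocol, delay and cost sample sizes | 4.42 | 0.933 | 35.1% |
| 0.03 | protocol, detection-rate clusters | 3.05 | 1.122 | 26.2% |
| 0.01 | assumption, not in the protocol | 1.68 | 1.511 | 13.1% |

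**4. Simulation check.** 20,000 null trials per setting, three districts against three, N = 416:

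| ICC | Patient-level t-test | Logistic regression, no district term | t-test on six district values (4 df) |
|---|---|---|---|
| 0.05 | 35.0% | 35.5% | 5.0–5.2% |
| 0.03 | 26.2% | 26.6% | 4.9–5.1% |
| 0.01 | 12.7% | 12.9% | 4.9–5.1% |

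The last column spans continuous and binary outcomes. The t-test column uses a continuous outcome and the logistic column a binary one, so the inflation does not depend on how delay is scaled.

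**5. Sensitivity.** If the 10% non-response allowance is used up, 416 / 1.10 = 378 patients remain, or 63 per district. DEFF is then 2.86 and 4.10, and the errors are 24.7% (ICC 0.03) and 33.3% (ICC 0.05). If the 40 clusters of 18 were themselves the randomised units, DEFF would be 1.51 and 1.85 and the errors 11.1% and 15.0%. That contradicts the randomisation section but still exceeds 5%.

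**6. Case detection rate.** Step 3 does not apply to an area-level ratio. A t-test on six district rates compares the units that were randomised, on 4 df, and holds about 5%, as the last column of step 4 illustrates. A t-test on 40 smaller units nested in six districts would again ignore the district. The protocol does not say which is meant. Logistic regression needs a yes/no outcome per record, and the ratio as defined does not supply one.

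**The case against.** The strongest reply is that the protocol does plan a clustered analysis. The abstract promises mixed models for the arm comparison, and the cost model explicitly allows for clustering. That stands for cost, where the fault is two competing methods and not the absence of a valid one. For delay, the abstract's general sentence conflicts with the detailed section, which limits the mixed model to cost. The two must be reconciled, and the abstract alone does not settle it.

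Second, logistic regression is described as a search for associated factors, not as the treatment comparison. That is fair, but the t-test is then the only arm comparison that the Data analysis section gives for delay.

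Third, the protocol gives no ICC specific to districts. Its 0.05 is a between-centre value, and its 0.03 goes with clusters averaging 18 people. Carrying them to districts is an assumption.

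A reader might infer more than the text supports:

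- **All three outcomes carry a 13–36% false-positive rate.** No. Cost has a clustered model, detection rate is an area-level ratio, and the 13% end needs an ICC that the protocol does not give.
- **The primary outcome cannot be tested validly.** No. A t-test on district rates is valid; the unit is simply not fixed.
- **The p < 0.25 screen could remove trial arm.** Nothing says that arm is one of the screened variables.
- **An exact randomisation test could not reach 0.05 with six districts.** No such test is planned.
- **Omitting a small-sample correction is a fault in itself.** That detail may be left to an analysis plan that is not shown.

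**Conclusion.** The point holds in three parts.

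- **Delay:** the Data analysis section names an arm comparison that does not match the randomisation. Run on patients, it would have a type I error of about 26% at ICC 0.03 and 35% at ICC 0.05, against a nominal 5%. This rests on six randomised districts, about 69 patients in each, and the protocol's ICCs applying at district level. At an assumed ICC of 0.01 it would be about 13%.
- **Cost:** a clustered model and an unclustered t-test stand side by side with no stated priority.
- **Case detection rate:** the unit of the t-test is not fixed, and logistic regression does not suit the outcome. No inflation figure can be attached, because one permissible reading is valid.

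This is not detail left to an analysis plan: the protocol names specific methods, and they conflict with its design and its abstract. It should be corrected before the arms are compared.

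**What to change.** Name one arm comparison per outcome, with the district as the cluster.

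- **Case detection rate:** compare the six district rates, or their baseline-to-endline changes, by a t-test on 4 df.
- **Delay and cost:** use either a comparison of district-level summaries on 4 df, or a mixed model with a district random effect and a small-sample correction suited to the outcome type. Satterthwaite and Kenward-Roger corrections belong to linear mixed models and do not carry over directly to binary versions of delay or catastrophic cost.
- Remove unclustered patient-level t-tests between arms.
- Keep the logistic factor analysis separate from the arm comparison, and do not apply it to the area-level rate.
- Reconcile the abstract, the cluster count in the detection-rate sample size section and the Data analysis section.

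This changes wording only: no new data are needed, and baseline collection is already planned. Confidence intervals will be wider and, with 4 df, only large effects will be detectable.

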#### Phase 4: The end-line evaluation

End-line outcome assessment will be done by trained assessors. The comparison will be done between the end-line and baseline outcomes (case detection rate, cost of TB, and diagnosis delay) between the intervention and control groups.

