### Control groups

The control sites will follow the existing passive case-finding system (self-referral patients to nearby health facilities that use the same national guidelines to treat TB). The findings obtained from the control groups will be compared with those obtained from the intervention groups. Finally, changes between the two groups will be assessed and concluded.

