### Outcomes of interest

The study will have three outcomes of interest. The primary outcome is the TB case detection rate. The secondary outcomes of interests are diagnosis delay and costs of TB care. The case detection rate will be expressed as percentage. The diagnosis delay will be defined as the time interval between the onset of symptoms and the confirmation of TB diagnosis, which includes patient delay and health system delay. The cost of TB care will include both direct and indirect costs of the patient for TB care and treatment as collected from the patients themselves and their medical records. Direct costs include out-of-pocket payments for medical services (counseling, drugs, laboratory tests, X-rays, and hospital stays) and non-medical services such as transportation, food, and accommodation costs.

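### The Abstract, the end-line and control-group text and the Data analysis section disagree on the primary analysis of case detection rate, and unranked within-arm paired tests stand beside the between-arm tests

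*Protocol article*

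**What the plan says.** The Outcomes of interest section is clear about the endpoint: "The primary outcome is the TB case detection rate". The Abstract words it as a change without saying against what: "The primary outcomes of interest will be an increase in case detection rate".

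The contrast is described differently in different places of the Protocol article:

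- **Abstract, Methods:** "Generalized linear mixed models will be used to compare the outcome of interest between the trial arms, with adjustment for baseline differences".
- **Phase 4, end-line evaluation:** "The comparison will be done between the end-line and baseline outcomes", with the intervention and control groups then set against each other.
- **Control groups:** "changes between the two groups will be assessed and concluded".
- **Data analysis, first paragraph:** "Comparisons of detection rate, diagnosis delay, and costs of TB care between and within the intervention and control groups", by independent-samples and paired t-tests respectively.
- **Data analysis, later paragraphs:** logistic regression for correlates of case detection, and a covariate-adjusted analysis of detection whose model is not named. The mixed model appears here for another outcome: "Generalized linear mixed models (GLMM) will be used to assess the impact of the intervention on the change of cost of TB care".

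The Data quality assurance section also foresees a before-after comparison in both arms. No sentence says which of these analyses decides the primary outcome.

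**The concern.** A randomised trial protects its conclusion only through the contrast between the randomised groups. A paired test inside one arm asks whether detection moved over the year. It does not ask whether the intervention moved it. Detection can rise everywhere for reasons unrelated to the trial, such as programme changes, better reporting or recovery of services. Pairing the same districts, or handling clustering correctly, does not cure this, because the question itself is not the causal one.

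The between-arm text is not settled either. The Abstract and the Data analysis section assign the mixed model to different outcomes. A comparison of changes, a comparison of levels and a baseline-adjusted comparison can give different answers with six districts. If the choice is made after the data are seen, the error rate of the primary conclusion is no longer that of one test.

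**Working it through.** **1. The passages side by side**

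| Place | Analysis of case detection rate | Between arms? | Uses baseline? |
|---|---|---|---|
| Abstract, Methods | Mixed model (if detection is the outcome meant) | Yes | Yes, by adjustment |
| Phase 4; Control groups | Change from baseline, compared between groups | Yes | Yes, by change |
| Data analysis | Independent t-test, time point not given | Yes | Not stated |
| Data analysis | Paired t-test | No | Yes, before-after |
| Data analysis | Covariate-adjusted analysis, model not named | Yes | Not stated |
| Data analysis | Mixed model | Assigned to cost | – |

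**2. Is there a planned figure that fixes the contrast?** No. The sample size section for detection takes all confirmed cases and gives no effect size, power or tested contrast. The two sizes with stated power belong to the secondary outcomes. With n per arm = [1.96√(2p̄q̄) + 0.842√(p₁q₁ + p₂q₂)]² / (p₁ − p₂)², they come out as follows:

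- Diagnosis delay, 59.9% v 45.9%: 199 per arm, 398 in total, × 1.10 = 438. The plan states 438.
- Catastrophic cost, 40% v 27%: 206 per arm, 412 in total, × 1.10 = 453.2. The plan states 453.

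Both reproduce, but neither says how detection is to be tested.

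**3. What the paired test estimates.** Let τ be the change common to all districts and θ the intervention effect. The expected change is τ + θ in the intervention arm and τ in the control arm. The between-arm difference in change is θ. The intervention-arm paired test is a test of τ + θ = 0, so with θ = 0 it tests τ.

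**4. Illustrative size**

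*Inputs from the document:*
- Three districts or towns per arm (Randomization and recruitment).
- Population about 2.6 million in 13 districts and 2 towns (Study settings; Randomization and recruitment), and 132 cases per 100,000 (Measurements). Expected cases per unit: 2,600,000/15 × 132/100,000 = 228.8.
- Starting detection 100% − 39% = 61% (Background, Amhara region).

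*Assumptions not in the document:* equal-sized units, Poisson counts, between-district SD of 5–15 points, the size of any shared rise, the extra district-to-district SD of change, and two-sided 0.05 for each test. There were 40,000 simulated trials per scenario, with no intervention effect. The tests were the paired t-test in the intervention arm (2 df), the t-test on end-line levels (4 df) and the t-test on changes (4 df).

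*No shared rise, no extra variation in change:* each test alone is significant in about 5% of trials, or 2.5% in the favourable direction. At least one of the three is significant in about 13% (12.7–13.0%). At least one favours the intervention in about 6.5% (6.4–6.6%).

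*Shared rise, intervention-arm paired test significant upwards:*

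| Shared rise | No extra SD of change | Extra SD 5 points | Extra SD 10 points |
|---|---|---|---|
| 5 points | 11% | 9% | 6% |
| 10 points | 26–27% | 20–21% | 13% |

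Either between-arm test stays at about 2.5% in the favourable direction throughout.

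The middle row can be checked by hand. With a 10-point rise and no extra variation, the Poisson SD of a district's change is √[(0.61 + 0.71)/228.8] = 7.6 points. The standard error of a mean of three is 7.6/√3 = 4.4 points, and the noncentrality is 10/4.4 = 2.3 on 2 df. An extra SD of 10 gives √(7.6² + 10²) = 12.6 points, a standard error of 7.3 and a noncentrality of 1.4. The false-rise rate falls accordingly.

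*A second set of assumptions* (normal rates, baseline SD 10, total SD of change 5–10 points, shared rise of 5–10 points) gives 8–47% for the paired test with three districts per arm. It gives 65–100% if the 24 and 16 clusters mentioned in the sample size section are the units. Between-arm contrasts again stay at about 2.5%.

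**The case against.** The strongest reply is that the document already points one way. The Abstract, Phase 4 and the Control groups section all describe a between-arm conclusion, and the last ties the conclusion to changes between groups. The paired test is planned in both arms, so an equal rise in control districts would be seen. This is also a condensed article, and ranking analyses is often left to an analysis plan, which is not shown here.

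Much of this stands. It rules out three stronger readings that a reader might infer:

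- **That no contrast is named at all.** Between-arm contrasts are named in several places. The fault is that they do not agree, and that the Data analysis section does not carry through the Abstract's model.
- **That a rise within the intervention arm would count as success.** No sentence says so. The simulated paired-test figures look at that test alone and ignore the other results that the plan would also produce.
- **That every analysis is judged at 0.05, or that the independent t-test is an end-line comparison.** In the Data analysis section, 0.05 is a significance threshold only for the multivariable logistic model. The t-test has no stated time point and could be read as a test of changes, which would merge two of the three simulated contrasts.

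With an assumed true effect of 20 points, end-line and change comparisons disagree on significance in 32–57% of simulated trials at between-district SD 5–15 points. That is mostly low power with three districts per arm. It is not an error rate, and this point does not rest on it.

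What the reply does not remove is a contradiction in stated text over the mixed model, and a non-randomised test prescribed for the primary outcome with no label. Neither is a detail merely left for later.

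**Conclusion.** The point holds as an inconsistency to be reconciled. The article gives the primary outcome at least three descriptions of its analysis and includes a within-arm test that cannot isolate the intervention. The direction of the risk follows from step 3 of the working and needs no simulation. Its size does depend on assumptions. The 13% (6.5% favourable) assumes a free choice among three distinct contrasts. The 6–26% assumes a shared rise of 5–10 points, and moves with how much district changes vary. These figures are illustrations and do not predict what this trial will do.

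It should be fixed before analysis. Because the text already leans to a between-arm conclusion, it is not a fatal fault in the design.

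**What to change.** In the Data analysis section, name one deciding analysis for case detection rate: a between-arm comparison at district level that uses the baseline rate, two-sided 0.05. Either of the document's own options would serve: the difference in change (Phase 4 and Control groups) or the baseline-adjusted comparison (Abstract). The choice must be made before end-line data are seen.

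Then:
- label the remaining between-arm analyses of detection as sensitivity analyses;
- report within-arm before-after changes descriptively, and state that they are not evidence of effect;
- say which outcomes the mixed model applies to, and make the Abstract, Phase 4, Control groups and Data analysis sections agree.

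This is a change of wording in the protocol or analysis plan and needs no further data or patients. The only loss is that a significant within-arm change can no longer be offered as support for the intervention.

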### Sample size determination

#### Sample size for TB diagnosis delay among tuberculosis patients

To estimate the effect of integrating traditional care with modern care on diagnosis delay, the sample size will be calculated using the two-sample comparison of proportions formula in STATA version 16. A chi-squared test with two independent samples will be used to calculate the sample size using diagnosis delay. By considering the previous study conducted in the Amhara region with the proportion of diagnosis delay P1 = 59.9% [24] and by assuming that the effect of the intervention on diagnosis delay decreased by 14% in the intervention group as compared to the control, P2 = 45.9%. By considering the probability of a type 1 error of 0.05, 95% CI, power of 80%, and a 10% non-response rate, the total sample size will be 438. Since the study is a multicenter, individually randomized trial, the design effect will be used. According to the multicenter design effect formula, the design effect formula, the $$\mathrm{design\ effect}=\frac{\upsigma {e}^{2}}{\sigma {e}^{2}+\sigma {B}^{2}}$$ = 1 − *ρ*. The majority of formulas applied to multicenter designs have a better relative accuracy (ICC less than 0.052) for designs including more than 10 centers. Assuming that randomized will be balanced and stratified on centers that have equal group sizes [37], assuming the variation between the centers will be 0.05, the design effect = 1 – *ρ* = 0.95. Therefore, the final sample size is calculated as sample size * design effect; 438 * 0.95 = 416 (208 for each arm).

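### For diagnosis delay, Data analysis names a t-test with no district term while the Abstract points to a mixed model; with three districts per arm the t-test is anti-conservative

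*Protocol article*

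**What the plan says.** Protocol article, Randomization and recruitment: "Randomization will be done at the district level". Six units are drawn and split evenly, the second half going to control: "three districts or town administrations will be randomly assigned to the intervention arm, and the other three districts or town administrations will be assigned to" [sentence continues].

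The Abstract (Methods) makes delay a named outcome: "the secondary outcomes of interest will be decreased diagnosis delays and catastrophic costs for TB patients". It then gives the analysis: "Generalized linear mixed models will be used to compare the outcome of interest between the trial arms, with adjustment for baseline differences".

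The Data analysis section says something different, in three statements:

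- Arm comparison: "Comparisons of detection rate, diagnosis delay, and costs of TB care between and within the intervention and control groups will be done using independent samples". The sentence goes on to pair this with paired-sample t-tests for the within-group part. No district term or other allowance for clustering is mentioned.
- Logistic regression: "Logistic regression analysis will be used to determine the factors associated with case detection rate and diagnosis delay". This comes with univariable screening at p < 0.25 and no cluster term.
- Mixed model: "Generalized linear mixed models (GLMM) will be used to assess the impact of the intervention on the change of cost of TB care". The justification given there is that it accommodates clustering and the pre/post correlation.

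The sample size for delay is worked out on individual patients with a chi-squared test: "By considering the probability of a type 1 error of 0.05, 95% CI, power of 80%, and a 10% non-response rate, the total sample size" comes to 438, reduced to 416 (208 per arm).

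**The concern.** Patients in one district share facilities, healers, distances and referral habits, so their delays are likely to be correlated. With only three districts per arm, chance differences between districts do not average out. A test that counts patients as independent underestimates the standard error of the arm difference and can read ordinary district variation as an effect of the intervention.

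The Data analysis section recognises clustering, but it names the remedy for cost only. Delay is also the first specific objective listed in the Background. If the section is followed literally, the p-value and confidence interval for delay are anti-conservative. If the Abstract is followed instead, they need not be. With both in the document, the method for delay is not fixed before the data are seen.

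**Working it through.** **Reproducing the plan's figure.** Inputs from the delay sample-size section: 59.9% against 45.9%, alpha 0.05 (taken as two-sided), power 80%. The two-proportion formula without continuity correction gives 199 per arm, 398 in total. Then 398 × 1.10 = 438, and 438 × 0.95 = 416, or 208 per arm. The stated figures reproduce, and they are counts of individual patients.

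**False-positive rate of a t-test that ignores district.**

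- Patients per district: m = 208 / 3 = 69.3.
- Variance inflation: DE = 1 + (m − 1) × ICC = 1 + 68.3 × ICC.
- Actual type I error of a nominal 5% test: 2 × [1 − Φ(1.96 / √DE)].

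The protocol gives no district-level ICC for delay. Its 0.05 is a between-center value and its 0.03 is for the detection rate. Both are borrowed here, with smaller values added to show the range.

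| District ICC (assumed) | DE | √DE (factor by which the interval is too narrow) | Type I error |
|---|---|---|---|
| 0.005 | 1.34 | 1.16 | 9% |
| 0.01 | 1.68 | 1.30 | 13% |
| 0.02 | 2.37 | 1.54 | 20% |
| 0.03 | 3.05 | 1.75 | 26% |
| 0.05 | 4.42 | 2.10 | 35% |

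**Simulation check** (3 districts per arm, 69 patients each, 8,000 runs per setting, continuous and binary outcomes). The unclustered t-test rejected about 26% to 27% at ICC 0.03 and about 36% at ICC 0.05. A t-test on the district means (3 against 3) held between 4.9% and 5.2% over ICC 0.01 to 0.05.

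**Cost.** With 428 patients, m = 214 / 3 = 71.3. DE is 3.11 at ICC 0.03 and 4.52 at ICC 0.05, so the t-test of cost would have a type I error of 27% and 36%.

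**Other cluster definition.** The detection-rate sample-size section speaks of 40 clusters averaging 18 individuals. If those were the randomised units, DE = 1 + 17 × ICC, which is 1.51 at ICC 0.03 and 1.85 at ICC 0.05. The type I error would be 11% and 15%.

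**Power of a district-level test for the planned effect.** The variance of the arm difference is (0.599 × 0.401 + 0.459 × 0.541) × DE / 208 = 0.4885 × DE / 208.

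- ICC 0.03: SE = 0.0846, noncentrality 0.14 / 0.0846 = 1.65.
- ICC 0.05: SE = 0.1018, noncentrality 0.14 / 0.1018 = 1.38.
- With 4 df (critical value 2.776), the noncentral t gives power of 25% and 19%. At ICC 0.01 it is 40%.

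**The case against.** Five points can fairly be made for the plan.

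1. **The Abstract promises mixed models for the outcome of interest and lists delay among those outcomes.** This stands. A reader might infer from the Data analysis section that delay gets no cluster-aware analysis anywhere, or that the mixed model is deliberately reserved for cost. The document does not support that: the section never says the model is only for cost. What is shown is a conflict between two places.

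2. **The logistic regression is not the test of the intervention.** This also stands. It is described as a search for associated factors. An arm odds ratio read from it would share the fault, but the plan does not present it as the arm comparison.

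3. **The unit of the t-test is not stated.** True, and the same sentence covers the detection rate, which is an aggregate quantity. For delay, however, the sizing is on patients and nothing mentions district summaries, so patient level is the natural reading.

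4. **The inflation depends on borrowed ICCs.** Correct. A reader might quote 26% to 35% as the trial's false-positive rate, but it holds only at a district ICC of 0.03 to 0.05 and only if the t-test is the analysis used. The lower ICCs and the 40-cluster reading reduce it, yet no case examined brings it back to 5%.

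5. **Commitment to the CONSORT cluster extension suggests a drafting slip.** That is plausible, but a reporting guideline does not choose the test, and the test that is named ignores the district.

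**Conclusion.** The point holds as a conflict between the Abstract and the Data analysis section, in which the method named for delay in the latter is anti-conservative. It is something the plan states, not a detail left to a separate analysis plan. The size, about 9% to 35% false positives across assumed district ICCs of 0.005 to 0.05, rests on three assumptions: a patient-level t-test, six districts as the randomised units, and about 69 patients per district. The unadjusted between-arm t-test of cost has the same fault and also competes with the mixed model named for that outcome. Because the error favours finding an effect and correcting it needs no new data, it should be settled before analysis.

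**What to change.** In the Data analysis section, name one analysis of the arm effect on delay that respects the district as the randomised unit. Either of these would do:

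- a t-test on six district summaries, with 4 df, or 3 df if adjusted for the district's baseline value; or
- a mixed model with a district random effect and a small-sample degrees-of-freedom correction.

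Apply the same rule to the between-arm comparison of cost, so that the unadjusted t-test no longer stands beside the mixed model. Reword the Abstract and the Data analysis section so that both name the chosen method. Add a sentence that the logistic regression is an associated-factors analysis and not a test of the intervention.

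The cost is wording, wider intervals and an open statement about power. For the planned reduction from 59.9% to 45.9%, a 4-df test has power of about 25% at ICC 0.03 and 19% at ICC 0.05, far below 80%. The protocol should report this together with the ICC it assumes.
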